## Abstract

**Background:**

Detained adolescents exhibit high rates of behavioral health needs, yet few receive treatment during detention or community re-entry. Once adolescents are released into the community, caregivers must mobilize significant resources and overcome barriers to facilitate their treatment engagement. Parenting stress is often heightened during this forced separation and the re-entry transition. Parenting stress is associated with greater perceived barriers to treatment and, for adolescents who begin treatment, less therapeutic change and premature treatment dropout. Interventions designed to support caregivers of detained adolescents in managing their stress while navigating the juvenile legal system are urgently needed, and mobile health (mHealth) interventions offer promising, scalable approaches. RAISE (Reducing pArentIng StrEss) is a web-based application co-designed with caregivers of detained adolescents to reduce caregiver stress and promote postrelease adolescent behavioral health services use.

**Objective:**

This study will evaluate the effectiveness of RAISE in reducing caregiver stress and promoting adolescent behavioral health services use following release from detention.

**Methods:**

A randomized controlled trial with 60 caregivers of detained adolescents (ages 12-17 years) across the United States will be conducted. Caregivers will be recruited through passive and active techniques and randomized to receive RAISE (intervention) or an informational brochure (comparison). Self-assessment questionnaires will be completed at baseline and 3- and 6-month follow-up timepoints. The fully automated RAISE intervention includes an 8-week stress reduction intervention, self-monitoring and affirmational SMS text messaging, and resources related to navigating the juvenile legal system. Assessments include empirically validated measures of parenting stress, mindful parenting, parenting self-efficacy, adolescent services use, motivation for youth treatment, caregiver behavioral health, sociodemographics, and RAISE usability (intervention only). Caregivers will also participate in a semistructured qualitative exit interview at the 3-month (postintervention) timepoint. Descriptive statistics will examine recruitment, randomization, assessment, retention, and application usability. Independent samples *t* tests and chi-square analyses will determine whether randomization was successful based on multiple background variables; group differences will be accounted for in outcome analyses. Regression analyses will be used for outcome analyses, with an intent-to-treat design; analyses will include intervention group as a predictor and control for the baseline level of the outcome, application usage, and demographic characteristics. Potential moderators and mediators of intervention effects will be explored.

**Results:**

We propose the enrollment of 60 caregivers by April 2025, final data collection by September 2025, and submission of main findings for publication in December 2025.

**Conclusions:**

This study will provide empirical evidence regarding the impact of an mHealth stress reduction intervention co-designed with caregivers of detained adolescents. Findings will be informative for legal systems regarding how best to support caregivers of detained adolescents and the impact of reducing caregiver stress on adolescents’ linkage to behavioral health services following their release into the community.

**Trial Registration:**

ClinicalTrials.gov NCT05032742; https://clinicaltrials.gov/study/NCT05032742

**International Registered Report Identifier (IRRID):**

DERR1-10.2196/67511

## Introduction

### Background

Although rates of youth incarceration have declined over the past decade, the most recent publicly available data show that in 2021, the United States incarcerated over 24,000 young people [1]. This relatively low number, compared to historical rates (eg, in 2019, there were over 35,000 youth detained), is in part due to the COVID-19 pandemic, which had significant impacts on juvenile legal system facilities and reporting of data related to youth in placement [1].

Detained adolescents are disproportionately male, from racially minoritized backgrounds, and most commonly incarcerated for delinquent (violent, property, etc) rather than status (ie, behaviors criminalized for minors but not adults) offenses [2]. About two-thirds of detained males and three-quarters of detained females have a diagnosable psychiatric condition [3], with nearly half meeting criteria for a substance use disorder. Many have co-occurring substance use and psychiatric disorders, increasing their risk for substance-related recidivism [4], persistent reoffending [5], and antisocial activity [6].

Behavioral health treatment is effective at improving adolescent behavioral health (eg, reducing substance use and improving mental health) and legal outcomes, with research consistently demonstrating that treatment involving adolescents and their caregivers is most efficacious in offsetting maladaptive trajectories of risk behavior [7,8]. Yet, few adolescents with behavioral health needs receive services or referrals during detention or community re-entry [9], and legally involved adolescents and their caregivers face multiple barriers to accessing community-based treatment. Adolescent behavioral health treatment access and engagement are multifaceted issues. At the individual level, adolescents and caregivers may experience stigma about accessing behavioral health services, not trust service providers, or may not feel services are needed [10,11]. At the structural level, factors such as lack of available providers, transportation, and insurance access can also impact access [10]. Ultimately, caregivers must often mobilize significant resources to facilitate adolescent engagement in community-based behavioral health treatment (transportation, childcare, etc); this can be challenging when juggling the stress of caring for a legally involved adolescent. As such, few legally involved adolescents in need of treatment actually receive any of the empirically based services available [9]. Detention is a critical window in which adolescents and their caregivers can be linked with treatment, yet as a nation, we are largely failing to use this opportunity.

### Parenting Stress

Among the potentially malleable factors contributing to adolescent treatment engagement is parenting stress (ie, stress reaction to demands of parenting), a well-documented impediment to treatment engagement, treatment progress, and a predictor of adverse youth outcomes such as substance misuse. Parent-child relationship (P-C-R) stress theory [12,13], one of the most widely tested and empirically supported parenting stress theories, posits that parenting stress arises from 3 domains: (1) parent (P); (2) child’s behavior (C); and (3) parent-child relationship (R). Each domain is associated with functional outcomes (eg, P with parent psychopathology [14,15], C with child behavior problems and psychopathology [16,17], R with parent-child relationship conflict [18,19]), which degrade the quality and effectiveness of parenting behavior and lead to increases in child emotional and behavioral problems. P-C-R theory proposes bidirectional effects (eg, child’s behavioral difficulty increases over time and parenting stress increases, resulting in further problems with parenting and child well-being; parent mental health leads to impaired parenting and increases child behavioral problems, which increases parenting stress). Caregivers’ reactions to the stress of parenting are key in propelling the process forward. For caregivers of legally involved adolescents, stress can be amplified by separation from their detained child and navigating the expectations imposed by the carceral system.

Parenting stress is associated with greater perceived barriers to treatment (eg, perceived relevance) [20], less therapeutic change among youth during treatment [21], and premature treatment dropout [20,22,23]. Highly stressed parents tend to report less parenting self-efficacy [24] and more negative parenting practices [25] that increase youth risk for substance misuse [26]. Higher parental stress has been associated with greater motivation for youth treatment (ie, recognition that the youth has a problem and caregiver readiness to participate in their treatment), particularly when caregivers perceive youth to have more severe symptoms [27]. Among caregivers of legally involved adolescents in the community, caregivers experiencing more mental health distress tend to be more likely to recognize when their child is experiencing a behavioral health problem [28]; however, for caregivers of adolescents who are mandated to treatment by the courts, recognition of youth behavioral health problems has been shown to be lower compared to those referred by other sources (self, school, etc) [27]. Caregivers of adolescents re-entering the community following detention face a myriad of stressors and demands, for example, ensuring their youth adheres to probation requirements (eg, can include enrollment in school, court-mandated community service, and court-mandated service participation). Among the range of problems that adolescents re-entering the community are facing, caregivers may be less likely to recognize the need for behavioral health treatment as a priority. Disrupting the parent-child relationship cycle by reducing parenting stress has the potential to increase caregivers’ self-efficacy to engage in effective parenting strategies needed to overcome barriers in facilitating adolescent treatment engagement and to recognize when their youth needs behavioral health intervention.

One promising method of reducing parenting stress is through mindfulness-based interventions [29]. Mindfulness, “the practice of focusing full attention on the present moment intentionally and without judgment” [30], is posited to reduce perceived and biological stress reactivity by increasing awareness of and ability to tolerate thoughts and emotions. Evidence suggests that in-person mindfulness-based parenting interventions increase mindfulness, decrease parenting stress [31,32], and improve parent-adolescent relationship quality among highly stressed parents [33]. Decreasing parenting stress, starting while adolescents are in detention, has the potential to enhance caregivers’ ability to facilitate adolescent engagement in community-based behavioral health treatment during re-entry; possible mechanisms of action (Figure 1) include increases in caregivers’ parenting self-efficacy (ie, beliefs about one’s ability to carry out parenting roles [34]) and motivation for adolescent-focused treatment.

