#### Hypotheses

We hypothesize that caregivers receiving the RAISE intervention will experience reductions in their parenting stress and that their adolescents will be more likely to initiate behavioral health services post release. We will explore hypothesized mechanisms of intervention impact (eg, mindful parenting, parenting self-efficacy, and motivation for youth treatment) as well as potential moderators (eg, gender, race, and ethnicity).

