##### Sociodemographic Characteristics

We will collect data on caregiver race, ethnicity, gender, education, income, and adolescent history of legal involvement.

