#### RAISE Effectiveness

Outcome analyses will focus on proximal caregiver-level outcomes, including mindful parenting, parenting stress, parenting self-efficacy, perceived barriers to youth treatment, and motivation for youth treatment. Secondary distal outcomes will include adolescent treatment initiation and retention. Linear regression will be used for continuous outcomes (ie, mindful parenting, parenting stress, perceived barriers to youth treatment, motivation for youth treatment), logistic regression for 3- and 6-month follow-up dichotomous outcomes (ie, treatment initiation and adherence to mandated treatment), and Poisson or negative binomial regressions for count outcomes (ie, number of treatment sessions attended). All analyses will include the intervention group as a predictor and control for baseline level of the outcome variable, application usage, and demographic characteristics (determined during preliminary analysis). Potential moderators and mediators of intervention effects will be explored using the PROCESS macro in SPSS, which uses a regression framework. Moderation analyses will involve computing interaction terms of intervention group (intervention vs comparison) by key demographic factors (eg, caregiver age, gender, race, mental health, substance use, and youth age, centered before computing interaction term for continuous variables). Mediational effects will examine the impact of intervention group on key proximal outcomes assessed at 3 months (ie, mindful parenting, parenting stress, parenting self-efficacy, perceived barriers to youth treatment, and motivation for youth treatment) and their impact on distal youth treatment engagement and retention outcomes assessed at 6 months. An “Intent to Treat” design, where all initially assigned to the intervention group are included in analyses, whether or not they used the intervention, will be used.

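### The exploratory mediation models leave the step from 3-month caregiver mediators to 6-month youth treatment open to confounding by youth severity, which is neither graded by a listed measure nor among the stated covariates

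*Protocol article*

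**What the plan says.** - **Mediation plan** (Protocol article, RAISE Effectiveness): "Mediational effects will examine the impact of intervention group on key proximal outcomes assessed at 3 months", and then "their impact on distal youth treatment engagement and retention outcomes assessed at 6 months". The mediators are mindful parenting, parenting stress, self-efficacy, perceived barriers and motivation. Their status is exploratory: "We will explore hypothesized mechanisms of intervention impact" (Hypotheses).
- **Covariates** (RAISE Effectiveness): all analyses are to "control for baseline level of the outcome variable, application usage, and demographic characteristics (determined during preliminary analysis").
- **Theory** (Parenting Stress): stress and child behavior feed each other, so that "behavioral difficulty increases over time and parenting stress increases, resulting in further problems with parenting and child well-being". Higher stress is also said to go with greater motivation for treatment, "particularly when caregivers perceive youth to have more severe symptoms".
- **Measures** (Quantitative Measures): none grades the adolescent's symptoms or substance use. The one symptom inventory, under Caregiver Behavioral Health, concerns the caregiver. The sociodemographic items are "caregiver race, ethnicity, gender, education, income, and adolescent history of legal involvement".

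**The concern.** Randomization makes the arms comparable, so the effect of RAISE on a 3-month mediator is protected. The second half of an indirect effect is not. It compares caregivers who differ in 3-month stress or motivation, and they may differ because their adolescents differ. On the article's own theory, a more difficult adolescent means a more stressed caregiver. If such adolescents are also more, or less, likely to be in treatment at 6 months, the mediator coefficient absorbs part of that difference.

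What is at stake is the reading of mechanism: whether lower stress or higher motivation explains any effect on treatment use. The Discussion presents self-efficacy and motivation as mechanisms, and the findings are to inform a larger trial. The stated covariates do not help here. One of them, application usage, arises after randomization and exists only in the RAISE arm, so it does not belong in a model meant to isolate the mediator.

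**Working it through.** **The plan's own figure.** Study Sample Size Determination gives power .62 for N = 60, α = .05, 4 predictors and f² = .15. With a noncentral F, u = 4, v = 60 − 4 − 1 = 55 and λ = .15 × 60 = 9, power is .6208. The figure reproduces. This point does not turn on it.

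**What the article supplies for each leg**

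| Leg | In the article? |
|---|---|
| Youth behavior → parenting stress | Stated, with effects in both directions (Parenting Stress) |
| Youth severity → motivation | Not stated as a cause; perceived severity strengthens the stress–motivation association (Parenting Stress) |
| Youth severity → treatment use | Not stated; the nearest text is that families "may not feel services are needed" (Background) |

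The strengths below are therefore assumptions, shown as ranges.

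**Linear scale.** Standardize the mediator within arm. Let b be the true mediator–outcome effect, c the severity–mediator correlation and d the severity–outcome effect. Without severity in the model, the coefficient is b + cd. Suppose the baseline mediator is added, it correlates ρ with the 3-month mediator, and severity is stable. The normal equations then give b + cd/(1 + ρ). With ρ = .6 the bias is cd/1.6.

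| Stress path, b = −.20 | cd | No severity | Plus baseline stress |
|---|---|---|---|
| c = .1, d = .1 | .01 | −.19 | −.19 |
| c = .3, d = .3 | .09 | −.11 | −.14 |
| c = .5, d = .4 | .20 | 0 | −.08 |
| c = .6, d = .5 | .30 | +.10 | −.01 |

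For motivation with no true effect (b = 0), c = d = .2 gives +.04 and c = .5, d = .4 gives +.20. With baseline motivation added these become +.03 and +.13. If severity lowers use, the signs turn: c = .3, d = −.3 gives −.20 − .09 = −.29 for stress and −.09 for motivation.

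**Binary treatment, severity changing after baseline.** S0 and S3 are stress at baseline and 3 months; U0 and U3 are severity, correlated 0.6; r is the severity–stress correlation. The model is S3 = 0.5·S0 + 0.7·r·U3 − 0.4·arm + error, and logit P(treatment) = −0.6 + ln(0.70)·S3 + ln(OR)·U3, where OR is the severity odds ratio per SD. Each scenario has n = 400,000; repeat runs differ by about 0.01 to 0.03. Entries are odds ratios per SD of S3, with truth 0.70.

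| Scenario | arm + S3 | + S0 | + S0 + U0 | + S0 + U3 |
|---|---|---|---|---|
| r = 0.4, OR 2 | 0.93 | 0.93 | 0.86 | 0.70 |
| r = 0.5, OR 2.5 | 1.09 | 1.09 | 0.98 | 0.70 |

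- Over r = 0.3–0.5 and OR 1.5–2.5, the arm + S3 model runs from 0.80 to 1.09.
- With weak confounding (r = 0.1–0.2, OR 1.2–1.3) it gives 0.71 to 0.74.
- If severity lowers use (r = 0.4, OR 0.5) it gives 0.56.
- A motivation-type mediator with no true effect gives 1.21 to 1.38 at severity OR 2.

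**Why 3-month severity is not a clean adjuster.** The simulation above lets severity affect stress but not the reverse, whereas the article states both directions. Let 3-month severity also rise by 0.2 or 0.4 per SD of stress, at r = 0.4 and OR 2. The total stress odds ratio becomes 0.70 × 2^0.2 = 0.80 or 0.70 × 2^0.4 = 0.92. The model adjusting for 3-month severity still returns 0.70, because it removes the part of the stress effect that runs through the youth's behavior.

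**What existing proxies can do.** Even fully measured baseline severity moves 0.93 only to 0.86. In a separate run, a crude yes/no proxy moved 0.94 to 0.92.

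**The case against.** **The missing leg.** No passage says that severity raises treatment use, and the sentence on motivation describes effect modification. That is right. The direction of the bias is therefore conditional, and a reader should not infer that the article's own theory makes severity a cause of both mediator and treatment. The first leg is stated, though, and it suffices to make confounding a live possibility.

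**Severity is not wholly unrecorded.** Need type is part of eligibility, adolescent legal history is collected, and pre-detention service use is recorded and may already enter as the baseline outcome. All youths must have an identified substance use need, which may narrow the spread. This stands against any claim that nothing is measured. But these items are ungraded and not current. The stress index and the problem-recognition subscale are also close to severity, but they are parts of the mediators themselves.

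**Exploratory, underpowered, and detail for an analysis plan.** The mediation is labelled exploratory. At n = 60 the sampling standard deviation of the log odds ratio is about 0.3 to 0.4, depending on covariates, against a bias of ln(0.93/0.70) = 0.28 in the moderate scenario. This limits the weight of the point. It does not dispose of it: the article does fix a covariate set for all analyses, and a later plan cannot adjust for a measure that was never collected. Bias also carries forward into the larger trial, where sampling error shrinks.

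**Conclusion.** The concern holds in limited form. The mediator-to-treatment step is unprotected, the stated covariates contain no youth-severity variable, and no graded youth-severity measure is listed. If severity raises service use, the stress path is attenuated, possibly to null, and the motivation path is inflated. If severity lowers use, both biases reverse. For a true odds ratio of 0.70 the range tried runs from 0.56 to 1.09, and from 0.71 to 0.74 when confounding is weak. All strengths are assumed; none comes from the article.

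Two stronger readings are tempting and not supported. The first is that the stress mechanism will be hidden or reversed. On the linear scale, a null or reversal needs cd of at least .20 when b = −.20, and there was no reversal in the grid once baseline stress was adjusted. In the changing-severity simulation, a clear reversal appeared only at the strongest corner. The second is that adjusting for 3-month severity is the correction. Under two-way effects it can remove part of the pathway under study.

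The comparison of randomized arms is unaffected. Only conclusions about mechanism are.

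**What to change.** In the models for 6-month treatment given a 3-month mediator:

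1. Drop application usage.
2. Adjust for the baseline value of that mediator. The text promises the baseline outcome, which for these models is service use and not stress or motivation.
3. Adjust for pre-randomization youth variables already obtained: need type at screening, adolescent legal history and pre-detention service use. State that they are weak proxies and remove little bias.
4. For each indirect effect, report how strong an unmeasured severity–mediator and severity–treatment association would have to be to remove or reverse it.
5. Describe indirect effects as associations.

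Caregiver-rated items on current youth symptoms, added mid-trial, are optional. Recruitment is under way, so the data would be partial. If they are used, show results with and without them and do not present the adjusted model as the corrected one.

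Cost: some wording, a short sensitivity analysis, and one or two more covariates in small exploratory models, with some loss of precision. Steps 1 to 5 need no new data and remain possible after data collection ends.

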**Figure 1 figure1:**

Hypothesized model of intervention effects.

### mHealth Technology Approaches to Intervention

Parenting stress is a malleable individual-level target that can be addressed using approaches that circumvent barriers to treatment access, such as digital mobile health (mHealth) technology. Research with postpartum mothers experiencing parenting stress and parents of primary school students provides initial support for the effectiveness of self-guided, web-based mindfulness and self-compassion training programs [35,36]. Increasing available providers, reducing the cost of services, and improving reliable transportation access can also enhance treatment accessibility but require intensive, long-term system and policy-level interventions.

Using mobile phones to deliver health (mHealth) interventions is a viable method for caregivers of legally involved adolescents, who commonly cite time, transportation, agency or program issues, and distrust of professionals as barriers to accessing in-person services [10]. mHealth technology refers to “the use of mobile devices, such as mobile phones, tablet computers, and personal digital assistants to provide medicine, public health, and health services” [37] and is an efficacious, low-cost way of reaching underserved populations to engage them in and deliver quality care [38]. mHealth circumvents many barriers caregivers of legally involved adolescents report, including transportation and time (eg, accessible from any internet-connected device at one’s convenience). mHealth is widely used and effective at increasing communication, monitoring, and education, to reduce the burden of diseases associated with poverty, to improve access to health services, clinical diagnosis, and treatment adherence, and for chronic disease management [39,40]. mHealth allows for instantaneous and portable access and, in some cases, direct communication with providers [41]. Research indicates caregivers of legally involved adolescents and juvenile legal system stakeholders are interested in mHealth treatment [2,42,43], making it a likely acceptable approach for them. Using mHealth apps with caregivers of legally involved adolescents is, therefore, one potentially efficacious way to reduce parenting stress, circumvent well-documented barriers to treatment, and ultimately increase adolescent engagement in community-based behavioral health treatment.

